### Population and sample size

Participants will be recruited through leaflets placed in audiology, and ear, nose and throat (ENT) departments, and any direct contacts made to the recruiting centers in response to publicity in the national media. Written informed consent will be obtained from each participant in accordance with the permissions granted. The primary outcome measure of treatment efficacy is the Tinnitus Handicap Questionnaire (THQ) [17], where the maximum score is 2,700. THQ data from a published study of tinnitus maskers were used to estimate the required sample size (two-sample *t*-test power analysis, performed in *R*). After a 12-week intervention, Henry *et al*. [18] found that a difference in mean THQ score of 194 between groups with a pooled standard deviation (SD) of 450 was considered significant, and represented a medium effect size. If we therefore assume a difference in mean THQ score of 250 between groups with a pooled SD of 425 as representative of a large effect size, then for a two-sided significance level of 0.05 and 80% power, it is estimated that 47 participants are required for each group. We assume a low drop-out rate of approximately 5% in 12 weeks and therefore a total of 100 participants will be recruited.

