#### Exclusion criteria

• Objective tinnitus, Ménière’s disease, temporomandibular joint disorder

• Pulsatile tinnitus

• Intermittent tinnitus

• Severe anxiety, >25 score on the Beck Anxiety Inventory (BAI) [20]

• Severe depression, >29 score on the Beck Depression Inventory (BDI-II) [20]

• Catastrophic tinnitus, score ≥78 on the THI

• Hearing aid wearers for less than 9 months, or long-term hearing aid wearers who have had prescription adjustments within last 3 months

• Pure-tone absolute hearing thresholds >70 dB on individual frequencies up to 8 kHz (unable to sufficiently hear the stimulus)

• Taking part in another trial during the 30 days before study start

• The individually tailored training stimulus is uncomfortable or not acceptable to the participant

Pure-tone audiometry will be conducted in a soundproof booth using the Unity 2 system (Siemens, Berlin, Germany) and HDA 200 headphones (Sennheiser, Wedemark, Germany), measuring hearing thresholds between 125 and 12,000 Hz.

Participants will be withdrawn from the trial at any point if they commence any other form of tinnitus therapy, or if following commencement of the study they report an adverse event. The definition of an adverse event in the context of this study is either: 1) since wearing the device tinnitus intrusiveness increases and makes it unbearable; or 2) a disease or symptom (unrelated to tinnitus) present at baseline worsens following the start of the study.

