### Secondary outcome measures

#### Questionnaires

The World Health Organization (WHO) Quality Of Life-BREF (WHOQOL-BREF) is a 26-item questionnaire measuring self-perceived quality of life in four domains (physical health, psychological, social relationships, environment) with test-retest reliability of 0.66 to 0.80 [25].

In the UK, the THI is the most common clinical tool used for diagnosis, and sometimes outcome assessment [26]. It is a 25-item measure of tinnitus severity with test-retest reliability of 0.93.

We will also add the Tinnitus Functional Index (TFI) questionnaire [27] to the assessment battery. This 25-item questionnaire was very recently developed as a sensitive measure of treatment-related change in tinnitus distress with a clinically significant change defined at 13 points. It is also a diagnostic tool for tinnitus severity with high test-retest reliability of 0.97.

Participants will also be provided with a paper diary and asked to log their daily use of the device, and note any experience or comment on its usability.

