### Safety analysis

Adverse events that occur during the trial will be recorded and reported according to the trial sponsor’s standard operating procedure (SOP) for medical device trials (Nottingham University Hospitals NHS Trust SOP 52).

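### The protocol's own definition of an adverse event leaves out new-onset symptoms, and the safety section supplies no wider one

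*Protocol article*

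**What the plan says.** The definition stands in the closing paragraph under Exclusion criteria, which deals with withdrawal. A participant leaves the trial on starting another tinnitus therapy, "or if following commencement of the study they report an adverse event". The next sentence opens "The definition of an adverse event in the context of this study is either" and gives two alternatives: "since wearing the device tinnitus intrusiveness increases and makes it unbearable", or "a disease or symptom (unrelated to tinnitus) present at baseline worsens following the start of the study".

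The Safety analysis section is one sentence: "Adverse events that occur during the trial will be recorded and reported according to the trial sponsor’s standard operating procedure (SOP) for medical device trials". It does not refer back to the definition, and it does not give another.

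One other place might pick up a complaint. Under Secondary outcome measures, Questionnaires, participants keep a paper diary of device use and are asked to "note any experience or comment on its usability". The diary is not described as a safety instrument.

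**The concern.** The usual purpose of an adverse event definition is to catch anything untoward that happens after treatment starts, and new symptoms are the core of it. This definition is written as a closed pair and presented as the meaning of the term for the whole study. Its second limb requires the complaint to have been there at baseline.

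The device uses in-ear earphones worn for 4 to 6 hours daily over 12 weeks, followed by a 24-week extension. Placebo participants wear the same device with a different tone sequence. Weeks 0 to 12 are therefore the only randomized comparison of harms between the two tone patterns. After that, the placebo group is unblinded and crosses over. If new-onset complaints are not recorded as adverse events in that window, a report of few adverse events could reflect the definition rather than the device.

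This is not detail left to a fuller document. An article may be silent on how adverse events are defined. This one states a definition, and the definition is too narrow for safety recording.

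**Working it through.** The point rests on reading the text. The plan gives no figure for it.

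**Step 1. Apply the two limbs to the possible cases.** The symptom examples are illustrations, not taken from the document.

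| Event after the start | Limb 1 (tinnitus, unbearable) | Limb 2 (non-tinnitus, present at baseline, worse) | Adverse event as defined? |
|---|---|---|---|
| Tinnitus increases and is unbearable | yes | no | yes |
| Tinnitus increases but is bearable | no | no (tinnitus excluded) | no |
| Headache present at baseline gets worse | no | yes | yes |
| Headache, dizziness or ear irritation, absent at baseline | no | no (not present at baseline) | no |

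Two of the four rows fall outside the definition.

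**Step 2. See whether another section captures the excluded rows.**

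- *Bearable worsening of tinnitus.* The THQ is the primary outcome. The THI, the TFI and the Tinnitus Tester measures of loudness, pitch and bandwidth are secondary. Efficacy analyses plans between-group comparisons of all of them at 12 weeks. This row is measured and compared, though not under the adverse event label.
- *New-onset non-tinnitus symptoms.* No outcome measure is aimed at them. The diary might pick up a comment, but nothing says that comments are coded or treated as events.

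**Step 3. Read the Safety analysis sentence both ways.**

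- If it uses the term as defined under Exclusion criteria, new-onset symptoms are not passed to the sponsor's procedure.
- If the procedure brings its own wider definition, new-onset symptoms are recorded, but the document then uses one term in two senses. Because the withdrawal sentence uses that term too, it becomes unclear which events lead to withdrawal.

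The procedure is not shown, so the document does not settle which reading applies. Either way the two sections need reconciling.

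**Step 4. What 50 per arm could show, under assumed incidences.** The sample size section asks for 47 per group with about 5% drop-out: 47 / 0.95 = 49.5, rounded up to 50 per group, 100 in total. This matches the stated total. With incidence p, the probability of at least one event among 50 is 1 − (1 − p)^50. No incidence is given in the document, so p is an assumption:

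| Assumed p | P(at least one in 50) |
|---|---|
| 1% | 0.395 |
| 2% | 0.636 |
| 3% | 0.782 |
| 5% | 0.923 |
| 6% | 0.955 |
| 10% | 0.995 |

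This describes the chance of seeing an event in one arm if it is recorded. It is not the power of a comparison between arms.

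**Step 5. Effect on the efficacy design.** The sample size uses "a difference in mean THQ score of 250 between groups with a pooled SD of 425". None of its inputs depends on the adverse event definition, so widening the definition for recording alone leaves the 100 participants unchanged.

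**The case against.** The strongest reply is that the definition sits directly after the withdrawal sentence and was probably meant to say which events end participation. On that view the sponsor's device-trial procedure governs recording, with its own definition, and nothing is lost. This is a fair reading and cannot be ruled out. It rules out two stronger conclusions that a reader might draw: that new-onset harms cannot be compared between arms, and that they would be counted none of the time. Both assume that an unseen procedure adds nothing. The reply does not remove the difficulty, because the text says it is defining the term for the study, not listing withdrawal triggers.

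A second reply is that worsening tinnitus is well covered. This stands in full. Bearable worsening is outside the label, but it is measured on graded scales and compared by group.

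A reader might also infer that tying adverse events to withdrawal discourages participants from reporting them. That is conjecture: the document does not say what participants are told about the withdrawal rule.

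Finally, questioning at each visit and tables of events by arm are details that a condensed article may leave to the full protocol or analysis plan. Their absence is not part of this point.

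**Conclusion.** The point holds in this form. Under the protocol's own definition a new-onset symptom is not an adverse event, and the Safety analysis section gives no wider definition. The document therefore gives no assurance that such harms are recorded or can be compared by arm. It does not show that they will be missed.

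The size is a matter of category, not of number: a whole class of events falls outside the definition, and how many there would be cannot be derived. The Step 4 probabilities rest on assumed incidences and on 50 participants per arm. The primary outcome, its analysis and the sample size are unaffected. What is at risk is participant safety and the meaning of any statement about how many adverse events occurred.

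**What to change.** 1. For safety recording, define an adverse event as any untoward sign or symptom that is new or worsened since baseline, whether or not it is thought related to the device.
2. State the withdrawal criteria as a separate list that does not serve as the definition of an adverse event. If the definition were widened while the withdrawal sentence still used the same term, the set of events leading to withdrawal would widen with it. No withdrawal rule is proposed here; the sponsor should say which is intended.
3. Reconcile the closing paragraph of Exclusion criteria with Safety analysis, so that one definition applies to recording and it agrees with the sponsor's procedure.

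The cost is a change of wording, and more minor events will be listed. The article says that the trial is recruiting, so the change should be dated. The report can then say under which definition earlier events were recorded.

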### Randomization and blinding

Randomized allocation to groups will be based on a minimization protocol (Minim) [21] and conducted by a researcher who is independent of the trial. Minimization will be used here to match groups for age: 18 to 49 years, 50 to 69 years, 70 or over years (categories based on statistics for moderate to severe hearing loss sourced from the Royal National Institute for Deaf People, now Action on Hearing Loss [22]), gender, hearing loss (PTA at 0.5, 1, 2, 4 kHz), and grade of tinnitus severity (using THI categories defined in [23]).

Participants will be randomly assigned initially to receive the treatment (Group 1) or placebo (Group 2) stimulation. After 12 weeks, participants in the placebo group will crossover to start receiving the treatment according to the intervention algorithm, and will follow the same protocol as initially delivered to Group 1.

The RCT phase of this study will be conducted double-blind. Participants will not know the group to which they are allocated (intervention or placebo). The researcher assessing outcomes will not know which group the participant was allocated to. The audiologists fitting and adjusting the device will be blind to group allocation since they will be unaware whether the device programming code supplied to them after the participant is randomized generates an intervention or placebo stimulus. All participants will receive the same information about the expected trial outcomes.

### Intervention

The CR® neuromodulation device is small, lightweight, and connected to a pair of custom in-ear earphones (Figure 2). The device will be fitted by an appropriately trained audiologist using a custom sound console to determine a pitch matching the participant’s tinnitus percept, and to calculate a unique sequence of tones around that pitch to be employed in the treatment protocol for each individual. The tones are presented by the device at a level that is only slightly higher than the hearing threshold for those tones, that is, a comfortable quiet level that should not interrupt the participant’s normal daily routine. Participants will be instructed to wear the device for 4 to 6 hours daily during the RCT stage. During the LTE stage, participants in the intervention group will be advised to wear the device for at least 4 hours daily.

**Figure 2 F2:**
[figure not shown]
**Image of the acoustic CR® neuromodulation device.** CR, coordinated reset.

### Placebo control

Participants in the placebo group will also receive the same device and be presented with a sequence of tones. The placebo tones will include frequencies in the 500 to 4,000 Hz range, but excluding frequencies around the tinnitus pitch. The placebo tones will also be delivered at a slower repetition rate and are predicted not to have the same therapeutic effect as the treatment stimulus. The placebo does, however, represent an active intervention, since the participant may experience some level of tinnitus masking while the device is worn.

### Device fitting procedure

The tinnitus assessment and the device programming procedure will be identical for all participants. The individual’s dominant tinnitus pitch is determined using an adaptive bracketing method. To first establish a ‘bracket’, pure tones from 500 to 12,000 Hz are presented to the individual in an ascending/descending sweep with a step size of 500 Hz, and participants select tones that border similarity to their tinnitus percept. Once this bracket has been established, a two-alternate forced-choice method is used to determine a dominant tinnitus pitch. Once a dominant pitch is reliably identified, the proprietary software uses an algorithm to program a set of four stimulation tones that span above and below the tinnitus pitch. Tones are then loudness matched, such that the participant subjectively equates each tone to be at a soft but audible listening level. All tones are compared against each other to ensure equal loudness.

All participants are prescribed with bilateral stimulation. Participants with unilateral tinnitus (experienced in one ear) will be prescribed bilateral stimulation with the same prescription. Participants with bilateral tinnitus that differs in pitch between ears by more than 200 Hz will require different stimulation prescriptions for each ear. All participants who do not perceive tinnitus to be in the ear will be prescribed bilateral stimulation with the same prescription (Figure 3).

**Figure 3 F3:**
[figure not shown]
**Device fitting protocol for differences in tinnitus percept between ears.** If tinnitus is identified as central (not in the ear) then only one ear need be assessed.

Participants will be reassessed at planned intervals over the 36 weeks of the trial (Figure 1), or at an interim interval if they experience a noticeable change in tinnitus pitch. The device prescription will be reassessed at each visit, and when there is a change in tinnitus pitch it will be adjusted accordingly. When a participant’s tinnitus pitch is increased beyond the output limits of the device, that is, tinnitus at or above 10.5 kHz, the participant will pause using the device for 2 weeks, and will then be reassessed. If at this assessment tinnitus remains at or above 10.5 kHz, the participant will be withdrawn from the trial.

### Primary outcome measure

The primary measure of efficacy will be change in THQ score between baseline and week 12. At the time of writing the protocol for the funding application, this questionnaire was one of the better validated measures of tinnitus severity, responsive to treatment-related change, and with a test-retest reliability of 0.93 [24]. The sample size is powered according to previous trial data using this measure [18].

### Secondary outcome measures

#### Questionnaires

The World Health Organization (WHO) Quality Of Life-BREF (WHOQOL-BREF) is a 26-item questionnaire measuring self-perceived quality of life in four domains (physical health, psychological, social relationships, environment) with test-retest reliability of 0.66 to 0.80 [25].

In the UK, the THI is the most common clinical tool used for diagnosis, and sometimes outcome assessment [26]. It is a 25-item measure of tinnitus severity with test-retest reliability of 0.93.

We will also add the Tinnitus Functional Index (TFI) questionnaire [27] to the assessment battery. This 25-item questionnaire was very recently developed as a sensitive measure of treatment-related change in tinnitus distress with a clinically significant change defined at 13 points. It is also a diagnostic tool for tinnitus severity with high test-retest reliability of 0.97.

Participants will also be provided with a paper diary and asked to log their daily use of the device, and note any experience or comment on its usability.

#### Psychoacoustic measures of tinnitus loudness and pitch

In addition to the pitch match performed as part of the device fitting procedure, baseline and changes in tinnitus quality (loudness, bandwidth, dominant pitch) will also be assessed using the Tinnitus Tester developed by Roberts *et al*. [11]. For loudness matching, participants adjust the level of 11 sound clips (center frequencies 500 to 12,000 Hz) until each one is perceived to equal that of the tinnitus sound. A sensation level is then calculated according to the matched value at a single frequency where there is little or no hearing loss and the frequency is distant from the dominant tinnitus pitch. Next, a tinnitus spectrum representing bandwidth is generated by asking participants to rate the likeness of the same 11 sounds to the pitch of their tinnitus, using a 100-point scale. Bandwidth can then be calculated as the SD of all frequencies in the tinnitus spectrum, where each frequency is weighted by its percentage likeness to the tinnitus pitch identified by the participant (compare [28]). A dominant tinnitus pitch is taken as the frequency in the spectrum with the highest likeness rating.

#### EEG spontaneous oscillatory activity

To assess changes in spontaneous oscillatory activity, EEG will be performed using a Neuroscan system (SynAmps^2^ model 8050, Compumedics Neuroscan, Charlotte, NC, USA) with 66 equidistant scalp electrodes. EEG will be conducted at baseline and at the end of the 12-week RCT for the first 50 participants (25 intervention, 25 placebo) attending Center 1 in Nottingham. At the 12-week visit, EEG will be performed after behavioral assessment, at a minimum 2-hour break from stimulation. For the recording, participants will be seated in a quiet, darkened soundproof booth, have their eyes open and be instructed to fix their gaze on a marker point in front of them. A central frontal electrode will be used as ground and a nose-tip electrode as reference, and two additional electrodes will be placed below the eyes to monitor eye movements. Electrode impedances will be maintained below 5 kΩ prior to the start of the recordings. EEG recordings will be collected over a continuous 10-minute period with a 0.5 to 200 Hz passband, and digitized at a 1,000 Hz sampling rate.

### Statistical methods, data analysis and reporting

Analysis will be performed to include all 100 participants who meet the study criteria and are fitted with the device. Participants leaving the study before its completion will not be replaced. Any missing data will be imputed using an expectation-maximization method, which assumes a normal distribution for the partially missing data and bases inferences on the likelihood under that distribution (maximum 25 iterations, performed in SPSS v16.0, IBM, Armonk, USA). Effect sizes will be calculated with Cohen’s *d* computed with the pooled SD of the two groups.

Following completion of the trial, the sponsor will use all reasonable endeavors to ensure the appropriate publication of the research. The manufacturer’s approval of the manuscript will be sought prior to submission. However, the investigators have the right to publish results of the statistical analysis, conducted according to the protocol, whether they are positive or negative, and whether they support or negate the commercial interests of the manufacturer.

Baseline characteristics of participants will be reported as descriptive statistics, including but not limited to age, gender, hearing levels, anxiety, depression, medication, tinnitus duration, tinnitus severity, tinnitus dominant pitch, and tinnitus loudness estimates. Comparisons between groups will assess the degree to which comparability of randomization was achieved.

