### Efficacy analyses

Our primary endpoint and first analysis of data will be the end of the 12-week RCT. Analysis will involve a summary of within- and between-group comparisons with respect to the primary and secondary outcome measures detailed above using paired *t*-test/McNemar’s test, *t*-test, and analysis of variance (ANOVA)/Kruskal-Wallis test analyses, as appropriate. In addition, (the simple and/or multiple) linear regression/general linear model/generalized linear model approaches will be performed, adjusting for the factors employed in minimizing participants to groups, as appropriate.

The second endpoint and planned analysis will be at the 24-week stage to examine the effect of 12 weeks’ intervention across all 100 participants. The final analysis of long-term effects will examine all 100 participants at trial completion (36 weeks).

Subgroup analyses will be performed to identify a participant population that demonstrates the most clinically significant improvement.

EEG recordings (only performed on half of the participants) will be analyzed using EEGLAB [29], an open source toolbox for advanced EEG analysis (Swartz Center for Computational Neuroscience (SCCN), University of California San Diego, CA, USA) run under MATLAB (The Mathworks, Natick, MA, USA). Pre-processed data (high- and low-pass filtering, offline epoching, artifact correction) will be further corrected for artifacts using independent component analysis (ICA) in EEGLAB [30]. Power analysis will be carried out in the EEGLAB, and obtained power spectra will be divided to analyze oscillatory activity in normalized EEG frequency bands. Analysis of sources of spontaneous oscillatory activity will also be conducted in EEGLAB (and/or standardized low resolution brain electromagnetic tomography (sLORETA)). Non-parametric statistical tests will be used to test for significant differences in any change in oscillatory activity between the placebo and intervention group. Within-group comparisons of activity recorded pre- and post-intervention will also be performed.

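### Single expectation-maximization imputation followed by complete-data tests ignores imputation uncertainty; whether the between-group result is then too liberal or diluted depends on whether arm is in the imputation model, which the protocol does not say

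*Protocol article*

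**What the plan says.** The section on statistical methods, data analysis and reporting fixes the missing-data rule: "Any missing data will be imputed using an expectation-maximization method, which assumes a normal distribution for the partially missing data". It goes on that the method "bases inferences on the likelihood under that distribution (maximum 25 iterations, performed in SPSS v16.0". The same section sets the analysis population: "Analysis will be performed to include all 100 participants who meet the study criteria and are fitted with the device". It bases the effect size on a Cohen's d "computed with the pooled SD of the two groups".

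The efficacy section then says "Analysis will involve a summary of within- and between-group comparisons with respect to the primary and secondary outcome measures detailed above", using paired and unpaired t-tests, ANOVA and their non-parametric or categorical counterparts, followed by linear models adjusted for the minimization factors. The primary outcome section states that "The primary measure of efficacy will be change in THQ score between baseline and week 12". Further analyses of all 100 participants are planned at 24 and 36 weeks.

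The article does not mention multiple imputation, residual noise added to imputed values, a variance correction or a sensitivity analysis. It does not list the variables in the imputation model, so it is not known whether arm is among them or whether imputation is run separately by arm.

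**The concern.** Expectation-maximization imputation replaces each missing score by one fitted value. Two things follow when the completed data go into a standard t-test or linear model. The test counts imputed participants as if they had been measured, so its sample size is too large. The fitted values also have no residual scatter, so the SD is too small, and that SD is the denominator of Cohen's d.

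The effect on the comparison between arms depends on the imputation model. With arm in it, the estimated difference is right on average but its standard error is too small. With arm out, both arms receive fitted values from one common regression, so the imputed participants contribute no arm difference and the treatment effect is pulled toward zero. The first case gives a test that rejects too often. The second gives a biased estimate and lost power. The rule covers the primary THQ comparison, so either outcome would affect the trial's main conclusion.

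**Working it through.** **The plan's own figure.** The sample size section says "assume a difference in mean THQ score of 250 between groups with a pooled SD of 425", and "for a two-sided significance level of 0.05 and 80% power, it is estimated that 47 participants are required for each group". The standardized difference is 250/425 = 0.588. The normal approximation gives 2 × (1.960 + 0.842)² / 0.588² ≈ 45.4, so 46 per group. The exact two-sample t solution is 46.35, so 47 (power 80.6%). With 5% drop-out, 47/0.95 = 49.5, so 50 per arm and 100 in total. The sample size reproduces and is not affected by this point.

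**Inputs for the check.**
- From the protocol: 50 per arm, difference 250, SD 425, two-sided 0.05.
- Assumed, because the protocol gives no figures: SD 425 at each visit, baseline–week 12 correlation r = 0.6, and a share m of week-12 scores missing completely at random in each arm.

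**Variance of the change score.** The part explained by baseline is E = (1 − r)² × 425² = 0.16 × 180,625 = 28,900. The residual part is R = (1 − r²) × 425² = 0.64 × 180,625 = 115,600. The SD of change is √144,500 = 380.

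**Arm in the imputation model.** Only the observed participants inform the residual part.
- True SE = √{2 × [E/50 + R/(50(1 − m))]}.
- SD after imputation = √[E + (1 − m)R], and reported SE = √{2 × [E + (1 − m)R]/50}.
- Approximate type I error = 2 × [1 − Φ(1.96 × reported SE / true SE)].

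**Arm left out.** The expected estimate is (1 − m) × 250. The residual part of its true variance is (1 − m)² × 2R/[50(1 − m)] = (1 − m) × 2R/50. That equals what the t-test reports when there is no effect, so the SE ratio is 1 and type I error stays at 5%.

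| Missing | Arm in: true SE | Arm in: reported SE | Ratio | Type I error | Arm out: expected estimate of 250 |
|---|---|---|---|---|---|
| 5% | 77.6 | 74.5 | 0.96 | 6.0% | 237.5 |
| 10% | 79.3 | 72.9 | 0.92 | 7.2% | 225 |
| 20% | 83.3 | 69.7 | 0.84 | 10.1% | 200 |

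**Simulation on the same inputs.** With arm in, type I error is 5.8%, 7.2% and 10.6% at 5, 10 and 20% missing, and at 20% the reported SE is 69 against a true 84. With arm out, type I error is nominal and 250 is estimated as 239, 226 and 199. These agree with the formulas.

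**Second simulation, other assumptions.** SD of change 425, correlation 0.5 and 0.8, 20,000 runs per setting:
- Arm in, t-test: type I error 0.062–0.064 at 6% missing, 0.073–0.075 at 10%, 0.099–0.109 at 20%. A baseline-adjusted model on the imputed data gives 0.065 at 6% and 0.118–0.122 at 20%. Mean d rises from 0.59 to 0.61 at 6% and 0.65 at 20%.
- Arm out: type I error 0.047–0.052 throughout. Mean d falls to 0.57 at 6% and 0.51–0.52 at 20%. t-test power is 80–81% at 6% and 71–73% at 20%.
- Within-group paired tests, no true change: 0.053–0.064 at 6% and 0.076–0.109 at 20%, so too liberal under either specification.

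**The case against.** **Reading the rule as inflating type I error and Cohen's d outright.** A reader might infer this. The protocol does not support it for the between-group comparison, because it holds only if arm is in the imputation model or imputation is run by arm. With arm out, type I error is nominal and d falls. This limits the claim about direction but does not rescue the rule, since both specifications give a wrong answer.

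**Size.** At the protocol's own drop-out of about 5% by week 12, type I error is about 6% and d about 0.61 instead of 0.59. The larger figures need 10–20% missing, which the protocol nowhere predicts. This stands, and it lowers the severity.

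**Weeks 24 and 36.** A reader might also infer that loss is known to be heavier there. Cumulative loss cannot fall, but no figure is given beyond week 12. The placebo group has by then crossed over, so those analyses are largely not a randomized two-arm contrast, and the between-group figures above do not measure error in them.

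**Condensed text.** The protocol does not literally say that values are filled once and treated as observed, and an article may leave the imputation variables to a fuller document. But the method, software, iteration limit, analysis set and tests are all stated, and a single fill-in followed by complete-data tests is their plain reading. The clause about basing inferences on the likelihood describes the imputation step. It does not make a later t-test on the filled data valid.

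**Conclusion.** The concern holds in conditional form. The stated rule gives invalid between-group inference whenever outcome scores are missing: too liberal, with d too large, if arm is in the imputation model; diluted, with d too small, if it is not. Under the assumptions above, type I error in the first case is about 6%, 7% and 10–11% at 5, 10 and 20% missing, and in the second a true 250 becomes about 239, 225 and 199. The defect is minor at the planned 5% loss by week 12 and material from about 10%. It should be fixed, but it does not by itself undermine the trial at the attrition the protocol expects.

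The numbers rest on assumed correlations and on data missing completely at random. The protocol withdraws participants for unbearable worsening of tinnitus, for starting another tinnitus therapy, and for a pitch that stays beyond the device limit. Some of these reasons may relate to outcome. Any bias from that is separate and is not included in these figures.

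**What to change.** Replace the expectation-maximization sentence with one of two analyses:
- a baseline-adjusted, likelihood-based analysis of the observed THQ scores, including arm and the minimization factors; or
- multiple imputation with arm in the imputation model, combined by Rubin's rules.

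Compute Cohen's d with an observed-data or model-based SD, not one taken from singly imputed data. Both analyses assume data missing at random, so add a sensitivity analysis for outcome-related loss.

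In the second simulation, the baseline-adjusted model on observed data held type I error at 0.050–0.052 for 6–30% missing. Its power for a difference of 250 was 84–90% at 6% missing and 78–85% at 20%. The cost is a change of wording, a different analysis routine and slightly wider intervals. Sample size, visits and data collection stay as they are.
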